#### Transcranial direct current stimulation

A tDCS Stimulator Model 101 (TCT Research Limited, Hong Kong, China) will be used to deliver a-tDCS and sham tDCS. For a-tDCS, a current of 2 mA will be delivered through two 50-cm^2^ electrodes, producing a current density of 0.04 mA/cm^2^. The anode will be soaked in saline and placed centrally over the left and right motor representation of the lower limb, as pre-determined with TMS, and secured with adjustable rubber straps. The cathode will be placed on the right trapezius muscle at the base of the neck, with Ten20 conductive gel (Weaver and Company, Aurora, CO, USA) used to secure the rubber electrode directly onto the skin. Figure 7 demonstrates the electrode montage. Stimulation will commence at the beginning of the training session and will be delivered for a duration of 20 minutes (typically ceasing approximately halfway through the session). Bioelectrical impedance will be monitored throughout the stimulation protocol and will not exceed 55 kΩ. Sham tDCS will involve an identical electrode montage, with stimulation ceasing after a 20-second ramp-up period to provide equivalent scalp sensation. A pseudo-stimulation feature built into the direct current stimulator allows for the device to be pre-programed to deliver sham stimulation while maintaining identical appearance, operation and screen prompts. This was conducted prior to each session by a laboratory assistant, enabling double-blinding of both researcher and participant.

**Fig. 7 Fig7:**
[figure not shown]
Example of electrode montage for anodal transcranial direct current stimulation

### Compliance requirements

Participants will be required to complete a minimum of 16 of the 18 scheduled training sessions (representing >85 % attendance). Testing of outcome measures (T0, T3, T6 and T9) will be completed within 72 h of the scheduled time point, determined from the commencement of the training programme.

### Outcome measures

#### Functional strength of the lower limb

Participants will perform 1RM tests to assess maximal voluntary strength of the lower limb muscles. A standard leg press and leg extension exercise will be performed on fixed pneumatic gym equipment (Air300; Keiser). Plantarflexion will be measured bilaterally on the seated leg press by placing the toes on the footplate and using the ankle dorsiflexion to press the plate forward while maintaining 180-degree knee extension. The unweighted movement distance is marked on the equipment, allowing the researcher to ensure that full range of movement is maintained during maximal attempts. Dorsiflexion will be measured unilaterally while the participant is seated with the heel positioned on a 25-cm step. A custom-made static strap weighted with an adjustable dumb-bell will be placed over the metatarsophalangeal joint, and the participant will be required to lift the dumb-bell smoothly through 45 degrees of dorsiflexion, measured by the researcher with a goniometer. All exercises have been chosen carefully to minimise any risk of falling or injury whilst being performed.

An initial starting resistance of approximately 20 % 1RM will be estimated by the researcher to familiarise the participant with the movement, and five to ten repetitions will be performed to provide a warm-up. The researcher will then select an appropriate resistance for a near-maximal effort, and the participant will be required to perform a single repetition of the exercise while maintaining correct technique. The resistance will be increased in 5–10 % increments as appropriate, until the participant can no longer perform a full repetition. Two minutes of rest will separate each attempt, and verbal encouragement will be provided. The highest resistance used to perform a successful repetition will be recorded as the 1RM in kilograms.

#### Functional assessments

Motor function specific to PD will be assessed with section III of the UPDRS-III. The same independent assessor will perform the test at all time points and will be blinded to the intervention group. The assessment will be performed at the same time of day and will precede all other tests to ensure fatigue does not confound performance.

A Timed Up-and-Go Test (TUG) will also be performed to assess motor function and speed [29]. Participants will be asked to rise from a 46-cm chair, walk around a plastic cone located 3 m away and return to the chair as quickly as possible. The arms of the chair may be used if necessary. The test ends when the participant assumes the original seated position, and time is recorded. Regular enclosed footwear will be worn, and customary walking aids may be used if required. The average time in seconds from three trials will serve as the TUG score.

The Berg Balance Scale will be used to assess functional balance [30]. The assessment will take approximately 20 minutes and will consist of 14 static and dynamic balance tasks which are scored from 0 to 4 by a trained exercise physiologist. The same assessor will perform the test at all time points and will be blinded to the intervention group. High validity and reliability of the Berg Balance Scale in neurological patient populations have previously been established [31].

The Five Times Sit-to-Stand Test (FTSTS) will be used to assess mobility and lower limb acceleration [32]. Participants will be seated in a 46-cm chair without armrests and will be asked to begin with their arms folded across the chest and their back upright against the backrest. Participants will perform five repetitions of moving from the seated position to standing, with the legs fully extended and hip and knee joints, as quickly as possible. The total time taken to complete five repetitions will be recorded in seconds. An inertial measurement unit (Nanotrak; Catapult Innovations, Docklands, Australia) worn on the right hip, sampling accelerations and gyrations at 100 Hz, will be used to determine vertical acceleration [33]. Previous researchers have reported high validity and reliability of the FTSTS in patients with PD [34].

#### Gait

Gait will be assessed using the ProtoKinetics Zeno 4.9-metre walkway (ZenoMetrics LLC, Peekskill, NY, USA). The walkway has a 2-foot-wide grid of pressure-sensing pads with a spatial resolution of 0.5 cm and a sampling frequency of 120 Hz. Participants will be asked to perform the walking trials at their preferred walking speed while wearing comfortable footwear. Two different gait conditions will be assessed: (1) normal walking and (2) walking while counting backward in 7s from a random three-digit number, termed *dual-task gait*. Three trials of each condition will be performed in random order. A trial begins by sitting silently on a chair for 30 seconds, then standing up and walking to a starting line located 1 m from the walkway. From the start line, the participant is asked to walk up and back four times to another line 1 m beyond the end of the walkway before returning to the seated position. The 30-second rest periods between each trial allow for accurate functional near-infrared spectroscopy (fNIRS) hemodynamic brain imaging (see ‘Functional near*-*infrared spectroscopy’ section below for details). The mean asymmetry and variability will be calculated using all of the steps of all of the trials for a given condition: step velocity (in meters/second), step duration (in seconds) step length (in centimetres), double support time (in seconds) and stride width (in centimetres). Step variability will be calculated on the basis of residuals, as suggested in previous literature [35]. Gait assessments using instrumented walkways have been shown to be repeatable in older adults [35, 36].

While undertaking the gait assessments, the participants will be asked to wear an inertial measurement unit on an elastic belt (Nanotrak) for sampling of accelerations and gyrations at 100 Hz at lumbar vertebrae L3–L5, in line with the spinous processes. Harmonic ratio [37] and multi-scale sample entropy will be calculated from the recorded vertical and resultant signals [38]. These inertial measurement unit-based variables have previously been shown to be repeatable [38].

#### Posturography

Static balance will be assessed with a 45-second bipedal standing test in three separate conditions: (1) eyes open, (2) eyes closed and (3) dual-task balance (eyes open while counting backwards in serial 7s from a random three-digit number). All tests will be conducted at preferred stance width, which will be recorded at baseline and maintained during all subsequent tests. A black dot (10-cm diameter) printed on white paper will be affixed 3 m in front of the participants at eye height, and the participants will be asked to fix their gaze on the dot while undertaking the eyes-open tests. Again, 30-second rest periods between each trial will be provided for concurrent fNIRS sampling. The measurement will be conducted on a portable force plate (AccuGait; AMTI, Watertown, MA, USA) sampling ground reaction forces at 500 Hz. Instantaneous centre of pressure will be calculated on the basis of recorded signals, and centre-of-pressure travel velocity (millimetres/second) will be calculated to represent static balance. The repeatability of centre-of-pressure travel analyses has been demonstrated in previous studies [39].

#### Transcranial magnetic stimulation and electromyography

Corticospinal excitability and intra-cortical inhibition of the tibialis anterior (TA) muscle will be assessed using two Magstim 200^2^ stimulators (Magstim, Whitland, UK) connected to a 110-mm, concave, double-cone coil (maximum output 1.4 T). The coil will be positioned with anterior-to-posterior current flow, and sites near the estimated right TA motor representation (approximately 1–3 cm lateral and anterior to the vertex) will be explored to determine the optimal site, which will be marked on the scalp with a permanent marker. Resting motor threshold (RMT) and active motor threshold (AMT) will be defined as the lowest stimulator output required to achieve an MEP with an amplitude greater than 0.05 mV and 0.20 mV in six of ten stimuli, respectively. Corticospinal excitability will be determined by delivering ten single-pulse stimuli at suprathreshold intensities of 1.3 × RMT and 1.5 × RMT. In accordance with previous literature [40], SICI will be determined by delivering ten paired-pulse stimuli, with the conditioning stimulus set at 0.8 × RMT, the test stimulus set at 1.3 × RMT, and an interstimulus interval of 3 milliseconds. Intra-cortical inhibition will be determined by calculating the SICI ratio (average paired-pulse MEP amplitude/average single-pulse MEP amplitude); thus, SICI ratio values closer to 1 will represent lower levels of intra-cortical inhibition, while SICI ratio values closer to 0 will represent higher levels of intra-cortical inhibition. The total of 30 stimuli (20 single pulses and 10 paired pulses) will be delivered in sets of 5 in a randomised order.

Once the TMS protocol has been completed with the TA muscle at rest, the same protocol will be repeated in an active muscle state while the participant maintains a low-level background contraction (10 % of maximum force). The participant’s maximal voluntary isometric contraction (MVIC) of the right TA will first be determined using a force transducer (LMD500; Futek, Irvine, CA, USA) mounted in a custom-made timber frame. The participant will be seated with the knee and ankle positioned at 90 degrees and the transducer positioned above the distal end of the metatarsals. The participant will be instructed to dorsiflex at the ankle with the base of the heel remaining on the floor, producing an isometric contraction against the force transducer. The peak force obtained from three maximal efforts with 2 minutes rest between attempts with the highest force output will be recorded as the participant’s MVIC. Verbal encouragement will be provided, and visual feedback of force will be visible on a monitor directly in front of the participant at eye level. To complete the TMS protocol in the active muscle condition, 10 % of the MVIC will be calculated and indicated by a line on the monitor. The participant will be asked to maintain the force feedback level with the line while TMS is delivered, with short rest periods (5–10 seconds) between each set of five stimuli. AMT will be defined as the lowest stimulator output required to achieve an MEP with an amplitude greater than 0.2 mV in six of ten stimuli.

Maximal compound waves (M-waves) will be collected during each session and used to normalise MEP responses. This method prevents any changes in peripheral muscle excitability acting as a confounder when determining corticospinal excitability [41]. A DS7A constant current electrical stimulator (Digitimer, Welwyn Garden City, UK) will be used to deliver supramaximal stimulation to the common peroneal nerve. The head of the fibula will be palpated, and a stimulating bar will be positioned directly inferior, with light pressure applied. Stimulation will be delivered at increasing current strengths until the muscle response reaches a plateau, then increased 10–20 % to ensure maximal stimulation is achieved. The largest resulting peak-to-peak muscle response will be reported as maximal M-wave amplitude. The M-wave will be obtained in both resting and active (10 % MVIC) muscle conditions and will be used to normalise resting and active MEPs, respectively.

All muscle responses (MEPs and M-waves) will be recorded using surface electromyography (sEMG). The area of electrode placement will be shaved to remove hair, rubbed with abrasive gel to remove dead skin, and then cleaned with 70 % isopropyl alcohol. Bipolar gel Ag-AgCl electrodes (8-mm diameter, model E258S; BIOPAC Systems, Goleta, CA, USA) will be placed over the TA muscle belly with an inter-electrode distance of 2 cm. A grounding electrode will be placed over the patella and used as a common reference. The electrode sites will be marked with a permanent marker, measured in reference to the tibial tuberosity, and photographed to ensure consistent electrode placement between sessions. All cables will be fastened with tape to prevent movement artifact. All sEMG signals (including MEPs) will be amplified (×1000) with band-pass filtering between 13 Hz and 1000 Hz, digitised online at 2 KHz for 500 milliseconds, and recorded and analysed using PowerLab 4/35 (ADInstruments, Bella Vista, Australia).

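### Read literally, the contracted-muscle SICI conditioning pulse is tied to resting threshold, which biases the active SICI ratio towards 1 in any participant whose active threshold is at or below 0.8 × RMT

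*Protocol article*

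**What the plan says.** All of the relevant text is in the Protocol article, under Transcranial magnetic stimulation and electromyography.

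- **Resting block, single pulses:** "delivering ten single-pulse stimuli at suprathreshold intensities of 1.3 × RMT and 1.5 × RMT".
- **Resting block, SICI:** paired pulses "with the conditioning stimulus set at 0.8 × RMT, the test stimulus set at 1.3 × RMT, and an interstimulus interval of 3 milliseconds". The ratio is mean paired-pulse MEP over mean single-pulse MEP, and "SICI ratio values closer to 1 will represent lower levels of intra-cortical inhibition", with values near 0 meaning more inhibition.
- **Thresholds:** RMT and AMT require an "MEP with an amplitude greater than 0.05 mV and 0.20 mV in six of ten stimuli, respectively".
- **Active block:** after the resting measurements, "the same protocol will be repeated in an active muscle state while the participant maintains a low-level background contraction", at 10 % of maximum force. No separate intensities are given. The AMT definition is then repeated: "AMT will be defined as the lowest stimulator output required to achieve an MEP with an amplitude greater than 0.2 mV".

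AMT is not named anywhere as the base for a stimulus intensity. Each block has 20 single and 10 paired stimuli, and none delivers the conditioning pulse alone.

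**The concern.** The SICI ratio is read as inhibition on the footing that the conditioning pulse changes the response to the test pulse without producing a response of its own. At rest, 0.8 × RMT lies below threshold by construction. During contraction the threshold that matters is AMT, and 0.8 × RMT lies below it only if AMT exceeds 0.8 × RMT. Otherwise the conditioning pulse evokes its own MEP 3 ms before the test pulse, and that response enters the numerator of the ratio.

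Augmented M1 inhibition is one of the stated hypotheses, and the Abstract lists neurophysiological function during movement execution among the outcomes. The bias runs towards less apparent inhibition, against the hypothesis. If training or stimulation lowered AMT relative to RMT, a participant could cross the 0.8 line between visits, and the active ratio would rise with no change in inhibition. The document does not show that such a shift occurs, but the design as written could not separate it from a real loss of inhibition.

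**Working it through.** **Inputs from the article.** Conditioning pulse 0.8 × RMT; test pulse 1.3 × RMT; single pulses 1.3 and 1.5 × RMT; AMT criterion above 0.20 mV in six of ten; RMT criterion above 0.05 mV in six of ten. AMT/RMT is not given.

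**Step 1: stimulus count.** 10 pulses × 2 single-pulse intensities + 10 paired = 30, which agrees with the stated total. No stimuli remain for the conditioning pulse alone, so a response to it could be neither measured nor subtracted.

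**Step 2: conditioning pulse in AMT units.** Under the literal reading this is 0.8 ÷ (AMT/RMT). The alternative anchor, 0.8 × AMT, is shown beside it in RMT units.

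| Assumed AMT/RMT | 0.8 × RMT, in AMT units | 0.8 × AMT, in RMT units |
|---|---|---|
| 0.70 | 1.14 | 0.56 |
| 0.75 | 1.07 | 0.60 |
| 0.80 | 1.00 | 0.64 |
| 0.85 | 0.94 | 0.68 |
| 0.90 | 0.89 | 0.72 |
| 1.00 | 0.80 | 0.80 |

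The literal pulse reaches AMT exactly when AMT/RMT ≤ 0.80. From there, provided responses do not become rarer as intensity rises, the article's own AMT definition implies that the conditioning pulse alone gives more than 0.2 mV in about six of ten trials or more.

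**Step 3: share of participants affected.** This rests wholly on assumption. If AMT/RMT is normal, the share is Φ((0.80 − mean)/SD).

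| Assumed mean | SD 0.05 | SD 0.08 |
|---|---|---|
| 0.75 | 84 % | 73 % |
| 0.80 | 50 % | 50 % |
| 0.85 | 16 % | 27 % |
| 0.90 | 2 % | 11 % |

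**Step 4: size of the bias in an affected participant.** As an illustration, assume the conditioning pulse adds 0.2 mV in 60 % of paired trials and that responses add. Then observed ratio = true ratio + (0.2 × 0.6) ÷ test MEP. For a true ratio of 0.40:

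- test MEP 1 mV: 0.40 + 0.12/1 = 0.52
- test MEP 2 mV: 0.40 + 0.12/2 = 0.46
- test MEP 4 mV: 0.40 + 0.12/4 = 0.43

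The shift is towards 1 and shrinks as the test response grows.

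**The case against.** The strongest reply is that repeating the protocol may mean using the same multipliers on the threshold of the new state. AMT is restated inside the description of the active block, which would make sense if it were the base there. This reading cannot be excluded, so a reader should not infer that the conditioning pulse is certainly 0.8 × RMT in practice. It has little positive support, however. AMT may be defined simply because it is an outcome; the Background treats motor threshold as an index of excitability in its own right. Where the authors want a state-specific reference they say so, as with the M-waves used to normalise resting and active MEPs. An operator following the written intensities would use RMT.

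Second, the problem may be rare. AMT has the stricter criterion (0.20 against 0.05 mV), which pushes AMT/RMT up, and the Background reports that MEP size does not increase during contraction in PD, which may do the same. Both points stand. They favour the less affected end of the assumed range but do not fix a value.

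Third, a reader might infer that the active ratio ceases to measure inhibition at all. The document does not support that. The ratio becomes a mixture, and the illustrated shifts are modest. A value above 1 needs something more extreme, such as a true ratio of 0.70, a 0.5 mV test MEP and a 0.2 mV response on every paired trial: 0.70 + 0.2/0.5 = 1.10.

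Fourth, changing the rule mid-trial has a cost. The Trial status section reports 17 completers and six participants in training. Switching those six would put two rules within one person's series and create an artificial time effect. Excluding visits by post-baseline AMT/RMT would select on something treatment may alter. Both objections are right, and they shape the remedy.

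**Conclusion.** The point holds in a limited form. As written, the active-block conditioning pulse is 0.8 × RMT, and for any participant with AMT/RMT ≤ 0.8 the active SICI ratio combines inhibition with direct recruitment, biased towards 1. That conditional statement follows from the article's own definitions. How many participants meet the condition is unknown: the 2 % to 84 % range reflects assumed means of 0.75 to 0.90 and SDs of 0.05 to 0.08, not trial data. The 0.43 to 0.52 illustration rests on additivity and on the chosen contamination.

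A reader might go further and conclude that the inhibition hypothesis as a whole, or the trial's main result, is compromised. It is not. Resting SICI bears on the same hypothesis and is unaffected. Gait speed, static balance and UPDRS-III at T6 are the primary outcomes, and neither they nor the sample size depend on this measure. The repair is still worth making, because it is cheap and the contamination cannot be removed afterwards.

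**What to change.** 1. State in the TMS section which threshold sets the active-block conditioning pulse. For participants not yet assessed at baseline, set it at 0.8 × the AMT measured at that visit.
2. Keep every participant who has already started on the rule used at T0, so that no one's series mixes rules.
3. Report AMT/RMT by arm and visit, and adjust for or stratify by the rule used.
4. For participants tested under the RMT rule, repeat the active-SICI analysis restricted to those whose baseline AMT exceeded 0.8 × RMT. Selecting on the baseline value avoids conditioning on something treatment may change.
5. If AMT was already the base in practice, correct the text to say so; steps 1 to 4 then fall away.

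**Cost.** A sentence or two in the procedure and one sensitivity analysis. AMT is already measured, so no stimuli or visits are added. The downside is two conditioning rules across the sample for this one secondary outcome.

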#### Functional near-infrared spectroscopy

Mechanisms underlying difficulties in dual-task gait and balance are largely unclear. However, the PFC, which is primarily involved in attention and executive function, is also involved in human balance and locomotion [42], which likely plays an important role. Although attention and executive function that depend on the PFC are often affected in PD [43–45], patients may rely more on the PFC because of reduced movement automaticity of dysfunctional basal ganglia circuits [46–48]. Consequently, altered functioning of the PFC during dual-task gait and balance in PD might explain the difficulties of patients with PD and therefore will be examined in this study using fNIRS.

fNIRS neuroimaging uses optical technology to measure the relative concentrations of oxygenated haemoglobin (O_2_Hb) and deoxygenated haemoglobin (HHb) in the cortical layer microcirculation [49], producing cortical activation data consistent with data obtained from functional magnetic resonance imaging [50, 51]. Portable fNIRS has successfully been used to measure PFC activation during dual-task walking in patients with PD [52] and in other populations [53–55]. A PortaLite™ fNIRS system (Artinis Medical Systems, Elst, The Netherlands) will be used to assess PFC activation during several tasks, including counting backwards in 7s from a random three-digit number while seated and during the simple and dual-task gait-and-balance assessments described in the previous section.

The PortaLite™ device has three transmitters and one receiver, with transmitter-receiver distances of 30, 35 and 40 mm. Near-infrared light is transmitted with two wavelengths, 760 nm and 850 nm, and data will be sampled with a frequency of 10 Hz. The PortaLite™ device uses wireless technology (Bluetooth, Kirkland, WA, USA), allowing participants to perform the tasks without restriction of wires. Since a previous preliminary study showed no significant differences between left- or right-side PFC activation during dual-task walking in PD [52] the PortaLite™ device will be placed on the left forehead F3 site using the international 10–20 electroencephalography system. This location will target the left Brodmann’s areas 9 and 10, which correspond to the dorsolateral and anterior PFC [56, 57]. The device will be shielded from ambient light by covering the forehead with a black piece of fabric. Oxysoft software (Artinis Medical Systems) will be used for data collection and analysis.

On the basis of different absorption spectra, concentration changes of O_2_Hb and HHb in the targeted PFC area will be calculated from the changes in detected light intensity. This is done using the modified Beer-Lambert law, assuming constant scattering [58]. The differential path length factor, which accounts for the increased distance travelled by light due to scattering, will be set to 6 for all participants. For analysis, O_2_Hb and HHb signals of the three channels (the three transmitter-receiver distances) will be averaged. The moving SD-based movement artifact reduction algorithm method will be used within each trial to remove movement artifacts and other noise from the fNIRS signals [59]. The threshold for artifact detection will be set to 0.45 for O_2_Hb and 0.18 for HHb [52], with a window length for moving SD calculation at 0.5 seconds and a window length for artifact correction (locally weighted scatterplot smoothing window) on 1 second. The fNIRS signals will then be linearly de-trended per trial and low-pass-filtered at 0.1 Hz to remove heart rate from the signals. To enable direct comparison of the different trials within each task, the filtered signals will be biased, using the average concentration of the 5 seconds before the ‘start’ instruction as a reference (zero). Then, individual trials will be averaged per task to create three mean time course signals per person, which will then be averaged over all participants. Finally, the peak and mean concentrations (O_2_Hb and HHb) during the task and rest periods will be calculated over all trials for all participants and then averaged for each of the tasks.

